### Analysis

Data will be analysed according to the intention to treat principle. In addition, on treatment analyses will be performed. Changes in primary and secondary outcome measures between intervention and control group will be analysed using both univariate and multivariate techniques. Models will be adjusted for age, gender and socio-economic status (SES), and baseline differences. Potential additional confounding factors and effect modifiers will be checked and, if necessary, included in the model. Since dependency between observations of subjects from the same general practice may exist as well as between repeated observations within persons, multilevel analyses will also be carried out.

All analyses will be performed for intervention and control group in total, as well as for DM and COPD separately.

In the economic evaluation the cost and effects of care as usual and MPI by a practice nurse will be calculated and compared. The cost-effectiveness ratio will be stated in terms of costs per improvement on the BDI, the cost-utility ratio will focus on the net cost per QALY gained. Ratios will be determined for the total patient population as well as for COPD or DM patients separately. Bootstrapping will be used to estimate confidence intervals for calculated ratios.

Descriptive statistics, Chi-square and t-tests will be used to analyse data from the process evaluation.

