### Power calculation

Assuming an α of 0.05, a 1 – β (power) of 0.90, a decrease of 18 percent of non-severe depression in the intervention group versus zero percent in the control group, 192 persons were needed [68]; 48 COPD and 48 DM patients in the intervention group and 48 COPD and 48 DM patients in the control group. We decided to recruit four groups of 90 patients (in total: 360), as we not only anticipated the potential need for sub-group specific analyses, but also anticipated attrition varying between 20 and 30 percent (e.g. due to refusals during the follow-up).

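### Bootstrap confidence intervals for the cost-effectiveness ratios lose their meaning if the effect difference is not clearly non-zero, most plausibly for QALYs and within a single illness

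*Protocol article*

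**What the plan says.** The Analysis section of the protocol article defines two ratios: one sets costs against improvement on the BDI, the other sets net costs against QALYs. It then fixes the populations: "Ratios will be determined for the total patient population as well as for COPD or DM patients separately". Uncertainty is handled in one sentence: "Bootstrapping will be used to estimate confidence intervals for calculated ratios". The section mentions no cost-effectiveness plane, acceptability curve or net benefit, and no rule for replicates with zero or negative effect.

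The only planning effect is in the Power calculation section and is binary: "a decrease of 18 percent of non-severe depression in the intervention group versus zero percent in the control group, 192 persons were needed". The same section "anticipated attrition varying between 20 and 30 percent" and sets recruitment at four groups of 90. No expected difference or standard deviation is given for the BDI, for EuroQol-based QALYs or for costs.

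**The concern.** The ratio is the cost difference divided by the effect difference. It jumps from large positive to large negative values as the effect difference passes through zero, so its numerical order is not an order of preference. A negative ratio arises when MPI is cheaper and better, and also when it is dearer and worse. A positive ratio arises when it is dearer and better, and also when it is cheaper and worse. If bootstrap replicates of the effect take both signs, limits from the sorted ratios mix opposite conclusions.

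Cost-effectiveness is part of the first objective (Background). The Future implementation section makes proven cost-effectiveness one of the conditions for implementation. The second objective asks whether the effect differs between illnesses, so the separate DM and COPD results must stay readable even if one illness shows little or no benefit. That is where a ratio interval is weakest.

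**Working it through.** **Inputs from the article.** Alpha 0.05, power 0.90, 18% versus 0%, 48 per arm within each illness, 90 recruited per arm within each illness (180 per arm overall), attrition 20-30%. After attrition this leaves 0.8 × 90 = 72 to 0.7 × 90 = 63 per arm per illness, and 144 to 126 per arm overall.

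**Reproducing the stated sample size.** Two proportions, unpooled variance, two-sided alpha 0.05:

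n = (1.960 + 1.282)² × 0.18 × 0.82 / 0.18² = 47.87, so 48 per arm. Applied within each illness, 4 × 48 = 192. The article's figure is reproduced.

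**Measure of the problem.** Orient the effect so that positive favours MPI. In one trial, the share of replicates with effect at or below zero is about Φ(−z), where z is the observed effect over its standard error. The share exceeds 2.5% when z < 1.96. From there on, replicates of the wrong sign are numerous enough to set a 95% limit. With expected value λ for z, the median share over trials is Φ(−λ), and the chance that more than 2.5% of replicates cross is Φ(1.96 − λ).

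**(a) Under the binary planning effect**, λ = 0.18 / √(0.18 × 0.82 / n):

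| n per arm | λ | Median share | Chance that share > 2.5% |
|---|---|---|---|
| 48 | 3.25 | 0.06% | 10% |
| 63 (one illness, 30% attrition) | 3.72 | 0.01% | 3.9% |
| 126 (overall, 30% attrition) | 5.26 | below 0.001% | 0.05% |

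**(b) Under assumed standardised effects d**, λ = d√(n/2). All d values are assumptions. Ranges run from 20% to 30% attrition.

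| d | Overall (144-126): median share | Overall: chance > 2.5% | Per illness (72-63): median share | Per illness: chance > 2.5% |
|---|---|---|---|---|
| 0.1 | 20-21% | 87-88% | 27-29% | 91-92% |
| 0.2 | 4.5-5.6% | 60-65% | 11.5-13.1% | 78-80% |
| 0.3 | 0.6-0.9% | 28-34% | 3.6-4.6% | 56-61% |
| 0.4 | 0.03-0.07% | 8-11% | 0.8-1.2% | 33-39% |
| 0.5 | below 0.01% | 1-2% | 0.1-0.3% | 15-20% |

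With no effect at all, λ = 0 and the chance is Φ(1.96) = 97.5% at any sample size.

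**What a limit then means.** Take d = 0.2 at 63 per arm, so effect/SE = 0.2 × √31.5 ≈ 1.1, and assume cost difference/SE = 1, with cost and effect independent. Cheaper and better: Φ(1.1) × Φ(−1) = 0.864 × 0.159 = 13.7% of replicates. Dearer and worse: Φ(−1.1) × Φ(1) = 0.136 × 0.841 = 11.4%. Both groups have negative ratios. In simulation the percentile interval ran from about −9 to +11 in SE units, and more than nine in ten of the replicates below the lower limit were dearer and worse. The limit that looks most favourable was set by the least favourable replicates.

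**Net benefit on the same replicates.** NB = willingness to pay × effect difference − cost difference has no denominator. In a simulation with assumed costs (difference 300, SD 4,000, 2,000 per SD of effect), its 95% interval covered 94.4-95.6% in every scenario tried.

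**The case against.** The strongest reply is that nothing in the article shows crossing to be likely. The effects in table (b) are assumed, and under the article's own planning effect crossing is rare even within one illness. This stands, and it rules out an unconditional claim that the intervals will fail. It does not show that they are safe: the planning effect is a change in the proportion with non-severe depression, whereas the two denominators are BDI improvement and QALYs. The sample size was not based on QALYs.

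A second reply is that a condensed article may leave the type of bootstrap interval, the plane and the acceptability curve to a fuller document. The article does not say that percentile limits will be used, and it also says costs and effects will be compared. That is fair for presentation details. But confidence intervals on the ratios are a stated choice, and a different bootstrap interval does not restore an order to ratios from opposite quadrants.

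Third, if the BDI difference is significant at two-sided 5%, fewer than about 2.5% of its replicates cross. So the cost-per-BDI ratio overall may well be unaffected. This stands and narrows the concern.

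A reader might infer more from two other figures:

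- Averaged over hypothetical trials, the wrong-sign share at d = 0.2 is 12-13% overall and 20-21% per illness. That average is pulled up by a skewed distribution and should not be set against a threshold that applies within one trial. The medians in table (b) are lower.
- Simulated percentile intervals for the ratio covered 98-99% at d = 0.1-0.2. That is conservative, not under-coverage. The harm is loss of meaning.

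**Conclusion.** The concern holds conditionally. The article commits to an interval that can be read only if the effect difference is clearly non-zero, for two ratios in three populations. With 20-30% attrition, the chance that more than 2.5% of replicates cross zero is 60-65% overall and 78-80% per illness at d = 0.2. At d = 0.4 per illness it is 33-39%, although the typical trial there has only about 1% of replicates crossing. Under the binary planning effect it is 3.9% at 63 per arm. The d values are assumptions and the calculations use a normal approximation. The concern is most plausible for QALYs and for single-illness ratios.

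Two stronger conclusions are tempting and not supported. One is that crossing is likely in this trial: the article gives no BDI, QALY or cost figures from which to say so. The other is that ratio intervals should be abandoned altogether: where the effect replicates are essentially all of one sign, the interval can be interpreted.

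**What to change.** Keep the bootstrap and change how its output is summarised:

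- Base inference on incremental net monetary benefit with a 95% CI over a stated range of willingness to pay, per QALY and per BDI point, and on the acceptability curve.
- Show the replicates on the cost-effectiveness plane with the share in each quadrant.
- Report each ratio as a point estimate. Add a ratio interval only where essentially all replicates have the same sign of effect.
- Compare DM and COPD by the difference in net benefit, with its interval.

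The same replicates serve and no new data are needed. The Progress of the study section says follow-up was still being collected, so the change could be made before results. The small cost is that a willingness-to-pay range must be chosen and justified, including one per BDI point, for which the article gives no value.

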### Power calculation

Assuming an α of 0.05, a 1 – β (power) of 0.90, a decrease of 18 percent of non-severe depression in the intervention group versus zero percent in the control group, 192 persons were needed [68]; 48 COPD and 48 DM patients in the intervention group and 48 COPD and 48 DM patients in the control group. We decided to recruit four groups of 90 patients (in total: 360), as we not only anticipated the potential need for sub-group specific analyses, but also anticipated attrition varying between 20 and 30 percent (e.g. due to refusals during the follow-up).

## Discussion

### Progress of the study

Based on experiences in the pilot study, we anticipated having to screen 3600 patients in order to include 360 patients. However, we had to increase the number of patients to be screened to reach this number. This was done because the percentage of patients eligible for the MINI interview was lower than in the pilot study. Furthermore, the percentage of patients refusing the MINI interview was higher than expected. To arrive at a gross number of 360 patients we had to screen a total number of 8326 patients. The response rate to the screening questionnaire was 67%. Eventually, 361 non-severely depressed patients were recruited in the study (DM: N = 184; COPD: N = 177). All interventions have been administered; currently follow-up data are being collected. Data collection will be complete in September 2006.

### Process evaluation

First results of the process evaluation indicate that patients' satisfaction with the intervention is high, and 96.5% of the patients who received the intervention reported to have benefited from the intervention.

### Future implementation

If this intervention proves to be effective in reducing depression and improving quality of life and proves to be cost-effective, implementation of the intervention in the health care system is considered and anticipated. An implementation and dissemination plan has been developed and is regularly being updated to the latest insights.
